## Outcome measures

The primary outcome will be the association of plasma 25(OH)D with the PGRs represented as the incremental areas under the curve (iAUCs) and peak values (PVs) in different ethnic groups. The secondary outcomes include the difference in iAUCs, PVs, and the following variables relating to vitD status between ethnic groups. C-reactive protein (CRP) is reported to have an inverse relationship with 25(OH)D, indicating an anti-inflammatory property of vitD (de Oliveira et al., 2017). The total cholesterol and high-density lipoprotein (HDL) have inverse and positive associations, respectively, with vitD status (Alkhatatbeh et al., 2019). BMI and body fat percentage are used as confounding factors of 25(OH)D (Grønborg et al., 2015) and PGRs to drinks (Dhaheri et al., 2010). PTH and calcium are closely related to vitD metabolism (Goltzman et al., 2018). The plasma 25(OH)D and PTH are measured using an AIA-900 immunoassay analyzer (Tosoh Bioscience, USA); CRP, calcium, total cholesterol, and HDL are measured using Horiba Pentra 400 Biochemistry Analyzer (Horiba, Japan). The body weight and fat percentage are measured with dual-frequency bioelectrical impedance analysis technology by TANITA DC-360 P (Tanita, Amsterdam) and body height by stadiometer. Dietary vitD intake will be analyzed by a 4-day estimated food diary analyzed using Nutritics software (Nutritics Ltd, Dublin). Knowledge and perception of vitD will be assessed by an online questionnaire (Appendix 2) collected via Qualtrics survey platform (Qualtrics, Provo, UT).

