**Methods:**

This acute randomized crossover trial will recruit healthy adults (n = 106) in East London between November 2023 and March 2025. Two test drinks are consumed by participants (a glucose drink containing 75 g glucose and pure orange juice) on different occasions. PGRs are monitored before and after drinking every 30 min for up to 2 h via finger prick. A fasting blood sample obtained via phlebotomy will be used for plasma 25(OH)D and relevant tests. A knowledge/perception questionnaire about vitD and a 4-day food diary (analyzing vitD dietary intake) will also be collected. Data will be analyzed using a multiple linear regression model adjusted by confounding factors (age, gender, body mass index, and body fat percentage).

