## Data analysis

The sample size was calculated using G*Power software (version 3.1.9.7; Heinrich Heine University, Düsseldorf, Germany), based on F-tests for ANOVA: repeated measures, between-subjects factors. This study aims to achieve an effect size of 0.25 in the PGRs among three ethnic groups, considering that the response is taken from five different time points with 30-min intervals for each person, and to achieve 80% power in the study, we will need 32 people in each group (n = 96 in total) at the 5% level of significance. The details of the sample size calculation can be found in Appendix 3. Considering the acute nature of the study, we believe 10% of the attention is sufficient; therefore, the target number of recruitments is 106 participants. Data normality will be assessed using the Kolmogorov–Smirnov test. Continuous variables with a normal distribution will be presented as means ± standard deviations, while non-normally distributed data will be reported as medians and interquartile ranges. Categorical data are presented as numbers and percentages. The iAUC is calculated using approximated trapezoidal numerical integration (Chlup et al., 2008), and only the incremental area above the fasting level will be included. The association of plasma 25(OH)D concentrations and the iAUCs and PVs, respectively, will be analyzed using a multiple linear regression model adjusted by age, gender (using dummy variables), BMI, and body fat percentages, including all participants, as well as in different ethnic groups. The iAUCs and PVs concentrations between ethnic groups after each drink consumption will be analyzed by one-way ANCOVA adjusted by confounding factors including fasting glucose concentration, age, sex, BMI, and body fat percentage. The correlation of iAUCs and PVs between the two drink consumptions is analyzed by Pearson's correlation to identify the difference in the pattern of PGRs to different drink consumptions. Other continuous variables (e.g. plasma 25(OH)D etc.) between ethnic groups will be analyzed by one-way ANCOVA adjusting confounding factors (age, gender, BMI and body fat percentage). Categorical variables, e.g. gender, the percentage of patients with vitD deficiency etc., are compared between ethnic groups via Chi-square tests. The statistical significance will be reported with a *P*-value (significance was set at *P* ≤ 0.05, two-tailed) and a 95% confidence interval. The statistical software IBM SPSS 29 will be used to analyze the data. The percentage of missing data is expected to be low based on our previous experience. Therefore, regression imputation is used to address missing data. Both intention-to-treat analysis and per-protocol analysis will be used for the data analysis.

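### The primary outcome is tested by 8 to 16 regressions, each at 5%, with no deciding test: if nothing is associated, at least one is significant in about 23–29% (8 tests) or 35–48% (16 tests) of studies

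*Protocol article*

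**What the plan says.** Under Outcome measures, the protocol article defines a single primary outcome: "The primary outcome will be the association of plasma 25(OH)D with the PGRs", with the responses "represented as the incremental areas under the curve (iAUCs) and peak values (PVs) in different ethnic groups". Differences between ethnic groups in the same measures are secondary.

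Under Data analysis, the primary association is handled by regression: "The association of plasma 25(OH)D concentrations and the iAUCs and PVs, respectively, will be analyzed using a multiple linear regression model". The covariates are age, gender, BMI and body fat percentage, and the models are fitted "including all participants, as well as in different ethnic groups".

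The Abstract (Methods) states that there are two drinks: "Two test drinks are consumed by participants (a glucose drink containing 75 g glucose and pure orange juice) on different occasions". The regression sentence does not mention the drinks. A per-drink analysis is written only for the secondary group comparison: "The iAUCs and PVs concentrations between ethnic groups after each drink consumption will be analyzed by one-way ANCOVA".

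The only threshold given for any test is "significance was set at *P* ≤ 0.05, two-tailed". The article states no hierarchy, co-primary rule or adjustment for the primary regressions.

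**The concern.** A primary outcome should yield one conclusion with a known error rate. Here it consists of several slopes, each with its own 5% test, and the article does not say which one settles the question. If the results are mixed, a significant slope for one measure, one drink or one ethnic group could be presented as the primary finding. The 5% stated for each test would then not be the error rate of the study's main claim.

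This matters because the Implications section expects the results to support education programmes, food fortification strategies and a later randomized trial. A chance finding in one ethnic group could be carried forward in that way.

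**Working it through.** **The plan's own figures.** The article states no familywise error rate, so there is none to reproduce. Its sample size supplies the N used below and does reproduce. For the between-subjects F-test with f = 0.25, 3 groups and 5 measurements, λ = f²·N·m / (1 + (m − 1)ρ). With N = 96 and an assumed ρ = 0.5 (not in the text shown), λ = 0.0625 × 96 × 5 / (1 + 4 × 0.5) = 30 / 3 = 10. On 2 and 93 degrees of freedom the power is 80.2%, which matches 32 per group and 96 in total.

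**Counting the tests.**
- Measures: 2 (iAUC and peak value), from Outcome measures and Data analysis.
- Populations: 4 (all participants, White, South Asian, African-Caribbean), from Data analysis.
- Drinks: 2 were given. Whether each has its own regression is not stated.

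One drink, or a combined response: 2 × 4 = 8. Drinks modelled separately: 2 × 4 × 2 = 16.

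**If the tests were independent.** P(at least one P ≤ 0.05) = 1 − 0.95^m.
- m = 8: 1 − 0.95⁸ = 33.7%
- m = 16: 1 − 0.95¹⁶ = 56.0%

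**Allowing for dependence.** The tests are not independent. iAUC and peak value come from the same curve, the same people take both drinks, and the pooled model contains the three groups. The familywise error was therefore simulated with no association anywhere: 32 per group, four covariates independent of the outcomes, and 4,000 runs per setting. The Monte Carlo standard error is at most √(0.5 × 0.5 / 4000) = 0.8 percentage points. The article gives no correlations. The assumed ranges are 0.5–0.9 between iAUC and peak value and 0.3–0.7 between drinks.

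| iAUC–PV | Between drinks | 16 tests | 8 tests (one drink) |
|---|---|---|---|
| 0.5 | 0.3 | 48.0% | 28.4% |
| 0.5 | 0.7 | 42.3% | 28.3% |
| 0.7 | 0.5 | 43.9% | 26.0% |
| 0.8 | 0.5 | 42.6% | 25.8% |
| 0.9 | 0.3 | 39.4% | 23.2% |
| 0.9 | 0.7 | 35.5% | 23.3% |

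Over the full grid the result is 35–48% for 16 tests and, allowing for simulation error, about 23–29% for 8.

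**Other counts.**
- Three ethnic groups without the pooled model, both drinks: 12 tests, 32–42%.
- Pooled model only, both measures and both drinks: 4 tests, 12–18%.
- The article also plans both intention-to-treat and per-protocol analyses. Counting both would give up to 32 tests, but the two sets overlap so heavily that the error would rise only a little. They are not counted here.

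**Effect of the remedies.** One named test keeps the error at 5%. Holm starts at 0.05/8 = 0.00625 or 0.05/16 = 0.003125. When no association exists, Holm makes a false rejection exactly when Bonferroni does. Bonferroni over 16 gave a simulated familywise error of 3.4–4.6%.

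**The case against.** **The number of tests is not fixed by the text.** This stands. A reader might infer that the plan commits to 16 slopes and a false-positive chance of roughly 40%. The regression sentence does not say so, because the words about each drink belong to the ANCOVA. Separate modelling is nevertheless the likelier reading. The objectives in the Introduction list the glucose-test response and the orange-juice response side by side, Data analysis correlates iAUC and peak value between the two drinks, and no combined response is defined. The count must still be given as 8 to 16.

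**The article sets no rule that any one significant slope makes the study positive.** This also stands. A reader might infer such a rule from the bare 5% threshold, but neither Outcome measures nor Data analysis states one. The percentages describe a risk that the wording leaves open, not a declared success criterion.

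**The detail may be in a fuller protocol or an SAP.** This holds in part. A multiplicity procedure could be there, and the 5% sentence may be a general reporting convention. The point does not rest on that missing detail. The article itself defines a primary outcome in several parts and states a threshold for it.

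**The study calls itself observational, and confidence intervals are promised with the P-values.** This softens the consequence, since familywise error matters less for an estimation study. But the primary analysis is not labelled exploratory, and a significance threshold is set for it.

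**Conclusion.** The concern holds in a bounded form. The primary outcome is tested by 8 to 16 regressions, each at a two-sided 5%, with no deciding test and no adjustment stated. If no association exists and any significant slope is reported as the primary result, the false-positive chance is about 23–29% for 8 tests and 35–48% for 16, against a nominal 5%. The ranges rest on N = 96 and on the assumed correlations, which the article does not give. The direction does not depend on them: even the four pooled tests alone give 12–18%. The study can proceed, but its main claim is not held at the stated 5% until this is settled.

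**What to change.** Before analysis, state whether the two drinks are modelled separately in the primary regressions, and then adopt one of two routes.

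- **(a) One primary test.** Name one measure, one drink and one population, tested at two-sided 5%; for example, the slope of the glucose-drink iAUC on 25(OH)D in all participants. Make the other slopes secondary, report them with 95% confidence intervals and label them exploratory.
- **(b) A primary family.** Keep the measure, drink and ethnic-group slopes as primary, list them, and apply Holm across the list.

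**Cost.** Neither route needs more participants, visits or measurements, but each is more than an edit of wording. Route (a) narrows the stated primary question, because the group-specific and orange-juice associations are demoted. Route (b) keeps that question but lowers the power for each slope; with 16 slopes the smallest P-value must reach 0.003125. Both leave fewer routes to a significant primary result. The article reports that no stage was complete at submission and that the statistician is blinded, so the choice could be recorded without knowledge of the results.

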## Data analysis

The sample size was calculated using G*Power software (version 3.1.9.7; Heinrich Heine University, Düsseldorf, Germany), based on F-tests for ANOVA: repeated measures, between-subjects factors. This study aims to achieve an effect size of 0.25 in the PGRs among three ethnic groups, considering that the response is taken from five different time points with 30-min intervals for each person, and to achieve 80% power in the study, we will need 32 people in each group (n = 96 in total) at the 5% level of significance. The details of the sample size calculation can be found in Appendix 3. Considering the acute nature of the study, we believe 10% of the attention is sufficient; therefore, the target number of recruitments is 106 participants. Data normality will be assessed using the Kolmogorov–Smirnov test. Continuous variables with a normal distribution will be presented as means ± standard deviations, while non-normally distributed data will be reported as medians and interquartile ranges. Categorical data are presented as numbers and percentages. The iAUC is calculated using approximated trapezoidal numerical integration (Chlup et al., 2008), and only the incremental area above the fasting level will be included. The association of plasma 25(OH)D concentrations and the iAUCs and PVs, respectively, will be analyzed using a multiple linear regression model adjusted by age, gender (using dummy variables), BMI, and body fat percentages, including all participants, as well as in different ethnic groups. The iAUCs and PVs concentrations between ethnic groups after each drink consumption will be analyzed by one-way ANCOVA adjusted by confounding factors including fasting glucose concentration, age, sex, BMI, and body fat percentage. The correlation of iAUCs and PVs between the two drink consumptions is analyzed by Pearson's correlation to identify the difference in the pattern of PGRs to different drink consumptions. Other continuous variables (e.g. plasma 25(OH)D etc.) between ethnic groups will be analyzed by one-way ANCOVA adjusting confounding factors (age, gender, BMI and body fat percentage). Categorical variables, e.g. gender, the percentage of patients with vitD deficiency etc., are compared between ethnic groups via Chi-square tests. The statistical significance will be reported with a *P*-value (significance was set at *P* ≤ 0.05, two-tailed) and a 95% confidence interval. The statistical software IBM SPSS 29 will be used to analyze the data. The percentage of missing data is expected to be low based on our previous experience. Therefore, regression imputation is used to address missing data. Both intention-to-treat analysis and per-protocol analysis will be used for the data analysis.

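### The 80% power claim belongs to a five-reading repeated-measures ANOVA that the plan does not run, and it carries over neither to the ethnic ANCOVA nor to the primary 25(OH)D regression

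*Protocol article*

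**What the plan says.** All references are to the protocol article.

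- **Sizing test** (Data analysis): the calculation is "based on F-tests for ANOVA: repeated measures, between-subjects factors".
- **Effect and design** (Data analysis): "This study aims to achieve an effect size of 0.25 in the PGRs among three ethnic groups". The calculation counts five glucose readings per person, half an hour apart.
- **Resulting size** (Data analysis): "to achieve 80% power in the study, we will need 32 people in each group (n = 96 in total"), with alpha of 0.05. The details are referred to Appendix 3.
- **Primary outcome** (Outcome measures): "The primary outcome will be the association of plasma 25(OH)D with the PGRs", the latter expressed as iAUC and PV, in the different ethnic groups. Data analysis assigns this to multiple linear regression adjusted for age, gender, BMI and body fat percentage, run in all participants and in each ethnic group.
- **Ethnic comparison** (Outcome measures): the difference in iAUC and PV between groups is a secondary outcome. Under Data analysis, iAUC and PV "between ethnic groups after each drink consumption will be analyzed by one-way ANCOVA", adjusted for fasting glucose, age, sex, BMI and body fat percentage.
- **iAUC** counts only area above the fasting level.

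No repeated-measures ANOVA appears among the analyses listed.

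**The concern.** A power figure describes one test of one effect. Here the test that was sized compares the three groups on the average of five readings, the fasting one included. The tests that will be run are a regression slope on 25(OH)D and a group comparison of one summary value per person. The 80% is therefore attached to none of them.

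The summary values are also not the quantity that was sized. iAUC subtracts the fasting level, so if one group ran higher by the same amount at all five readings, the sized test would see that difference and the unadjusted iAUC would not. PV is a maximum, not a mean.

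What is at stake is how null results are read. The article expects the findings to inform a later randomized trial and to reach policymakers. The within-group regressions rest on about 32 people each. If readers take 80% as the power of the study, they may read a null slope in one ethnic group as evidence of no association.

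**Working it through.** **Inputs.** From Data analysis: f = 0.25 (read as Cohen's f, the ANOVA effect size in the named software), k = 3 groups, m = 5 readings, N = 96, alpha = 0.05. Assumed: correlation rho among readings, because Appendix 3 is not shown. All powers are from the noncentral F distribution with noncentrality lambda.

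**1. The plan's own figure.** For the between-subjects factor, lambda = f² × N × m / [1 + (m − 1) × rho], with df (k − 1, N − k).

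With rho = 0.5: lambda = 0.0625 × 96 × 5 / 3 = 10.0, df (2, 93), power 80.2%. In equal groups, 96 is the smallest N that reaches 80%, so the figure reproduces. It depends on rho:

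| rho | Required N | Power at N = 96 |
|---|---|---|
| 0.3 | 72 | 91% |
| 0.5 | 96 | 80% |
| 0.6 | 108 | 75% |
| 0.7 | 123 | 70% |

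**2. The planned ethnic ANCOVA, one value per person.** Here lambda = f² × N / (1 − R²), where R² is the share of within-group variance that the covariates explain. With five covariates, df = (2, N − 8).

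- Effect detectable with 80% power at N = 96, R² = 0: f = 0.32.
- f = 0.25 placed directly on iAUC or PV, R² = 0: lambda = 0.0625 × 96 = 6.0, power 57% (62% if all 106 complete). 80% would need N = 159.
- Same f with R² = 0.2: lambda = 7.5, power 67%. With R² = 0.4: lambda = 10.0, power 80%.

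**3. What if 0.25 is the effect at a single reading?** The formula in step 1 scales f that way. The f on the five-reading mean is then 0.25 × √(5/3) = 0.32, which is why that test reaches 80%.

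For iAUC, take the signed version (dips below fasting not truncated), unit SD at each reading, rho = 0.5, adjustment for fasting glucose, and no gain from the other covariates. In units of one 30-min interval, the four post-drink readings have weights 1, 1, 1 and 0.5, which sum to 3.5. Given the fasting value, each reading has variance 1 − 0.25 = 0.75 and each pair has covariance 0.5 − 0.25 = 0.25. The residual variance is 0.75 × 3.25 + 0.25 × (12.25 − 3.25) = 4.69, so the SD is 2.165.

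- Difference at the post-drink readings only: f = 0.25 × 3.5 / 2.165 = 0.40, lambda = 15.7, power about 95%.
- Same difference at all five readings: adjustment for fasting removes half of it, so f = 0.25 × 1.75 / 2.165 = 0.20, lambda = 3.9, power about 40%.

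PV has no such closed form. Its power would have to be simulated under an assumed glucose profile.

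**4. The primary regression.** There are five predictors (25(OH)D, age, gender, BMI, body fat percentage). One coefficient is tested: f² = r² / (1 − r²) with r the partial correlation, lambda = f² × n, df (1, n − 6).

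| n | f² for 80% power | Partial r for 80% power | Power at partial r = 0.25 |
|---|---|---|---|
| 96 (pooled) | 0.084 | 0.28 | 71% |
| 32 (one group) | 0.265 | 0.46 | 29% |

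The partial r of 0.25 is only illustrative. The documents give no expected association.

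**The case against.** The strongest objection concerns the ethnic comparison. Step 2 might lead a reader to infer that the ANCOVA simply has 57% power, a shortfall of 23 points (80 − 57). The documents do not support that. The 57% moves an effect scaled to a single reading unchanged onto a summary of several readings, and it credits the covariates with nothing although fasting glucose is one of them. Step 3 shows that, at one and the same correlation, power for iAUC is about 95% or about 40% depending only on where the groups differ. A between-subjects main effect covers both patterns. This part of the objection stands in full: the 57% is one conditional value, and the uniform-shift argument takes an unfavourable case.

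It can also be said that the 80% is claimed only for glycemic differences among ethnic groups, which the article's aim also names, and that Appendix 3 may hold more. Both are fair limits. The claim that the primary regression lacks a power basis can be made only of the shown text. The mismatch itself does not depend on Appendix 3, because Data analysis names the sizing test, its effect and its number of readings, and then lists other tests.

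Finally, a reader might want the within-group regressions labelled exploratory. The primary outcome is defined in the different ethnic groups, so that label would demote part of it. The low power calls for a statement of what can be detected, not for a change of status.

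**Conclusion.** The point holds as a mismatch between the sample-size calculation and the planned analyses. It is not an arithmetic error: 96 is correct for the test named, given a correlation of about 0.5.

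The stated 80% carries over to no planned analysis. The ethnic ANCOVA has 80% power for f of about 0.32 on iAUC or PV with no covariate gain. Whether the protocol's 0.25 amounts to more or less than that depends on the shape of the glucose difference and on the covariates, and the shown text settles neither. For the primary regression, 80% power requires a partial correlation of about 0.28 pooled and about 0.46 within a group. These figures assume five predictors, 96 evaluable participants in equal groups and alpha of 0.05 for each test.

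The firmest consequence lies in the within-group regressions, where only large associations are detectable.

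**What to change.** Keep the recruited number and restate the sample-size paragraph, with Appendix 3 brought into line:

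1. Give the effect detectable with 80% power in the primary regression with five predictors: partial r of about 0.28 pooled (n = 96) and about 0.46 within an ethnic group of 32.
2. For the ANCOVA, replace the unqualified 80% at 0.25 with the detectable f of about 0.32 on iAUC or PV, and state its assumptions (one value per person, 96 evaluable, no covariate gain). Do not print 57% as the power of this analysis.
3. State that the within-group regressions can detect only large associations, so that a null result there is not read as no association.

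The cost is a rewritten paragraph and a less favourable power statement. No participants are added and no planned analysis changes.

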VitD deficiency in ethnic minorities in the UK is well known and is described as an unrecognized epidemic (Darling, 2020). In the UK, 50% of SAs and 33% of Black ACs demonstrate vitD deficiency, whereas 17.5% of White Caucasians do (Sutherland et al., 2021), which is primarily due to more subcutaneous pigmentation that absorbs ultraviolet B from sunlight and reduces vitD production in the skin and at high latitudes in the UK (Yousef et al., 2023). This situation is worse in East London. In Tower Hamlets, a borough of East London, 80–97% of the residents are thought to have vitD deficiency, significantly higher than the national population at 50% (Towerhamlets.gov.uk, 2017). An inverse association of serum 25(OH)D levels with insulin resistance was observed in healthy adults (Yin et al., 2022) and diabetic patients (Abubaker et al., 2022). Recent evidence from systematic reviews and meta-analyses of randomized controlled trials (RCTs) suggests that vitD supplementation may help reduce fasting plasma glucose concentrations, HbA1c levels, and insulin resistance in patients with T2DM (Afraie et al., 2024; Farahmand et al., 2023). However, little evidence is available that focuses on ethnic minority groups or residents in East London, indicating that AC and SA communities are underrepresented in the evidence base concerning diabetes and vitD.

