## Limitations and future perspectives

There are several limitations to this proposal. Firstly, the use of multiple finger-prick tests to measure postprandial blood glucose concentrations at 30-min intervals may miss the actual peak glucose value. Using 15-min sampling interval or continuous glucose monitoring (CGM) (Shields et al., 2024) would obtain more precise PGRs. Secondly, the proposal focuses on participants residing in East London; therefore, findings related to knowledge and perceptions of vitD, dietary intake, and the prevalence of deficiency may have limited generalizability to populations outside of this geographic area. In future studies, CGM (Shields et al., 2024) could replace finger-prick testing to assess PGRs following meal or drink consumption. This approach would provide more accurate and comprehensive data while reducing participant burden, provided budget constraints are not a limitation. Additionally, a large-scale study involving a more representative sample of diverse ethnic groups recruited from multiple London boroughs is warranted to enhance the generalizability of the findings. Data management can be found in Appendix 4 and timelines (Gantt Chart) can be found in Figure 2.

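### The primary regression of peak glucose on 25(OH)D omits fasting glucose, so its slope mixes a fasting with a postprandial association

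*Protocol article*

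**What the plan says.** All references are to the protocol article.

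- **Outcome measures:** "The primary outcome will be the association of plasma 25(OH)D with the PGRs represented as the incremental areas under the curve" and peak values, in different ethnic groups. Differences in iAUC and PV between ethnic groups are secondary.
- **Data analysis, primary model:** a "multiple linear regression model adjusted by age, gender (using dummy variables), BMI, and body fat percentages, including all participants", and also within each ethnic group. The Methods paragraph of the abstract gives the same four covariates: "multiple linear regression model adjusted by confounding factors (age, gender, body mass index, and body fat percentage".
- **Data analysis, next sentence:** iAUC and PV are compared between ethnic groups by "one-way ANCOVA adjusted by confounding factors including fasting glucose concentration, age, sex, BMI, and body fat percentage".
- **Data analysis, definition of iAUC:** "only the incremental area above the fasting level will be included". No such subtraction is stated for PV. The Limitations section says that 30-minute sampling "may miss the actual peak glucose value", which also reads as an absolute concentration.
- **Study design:** glucose is measured at 0 min at each visit, so a same-visit fasting value exists for both drinks.

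No reason is given for including fasting glucose in one model of PV and not in the other.

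**The concern.** The stated aim concerns the postprandial response. An absolute peak is the fasting level plus the rise after the drink. If people with lower 25(OH)D start from a higher fasting glucose, their peak is higher even when their rise is the same. The planned PV regression cannot tell this apart from a larger rise, and the result would be presented as a postprandial association.

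PV is one of the two measures in the primary outcome. The article describes the study as observational in nature (Implications of the study), so the choice of covariates largely determines what the primary slope means. The plan itself treats fasting glucose as relevant to PV, but only in the secondary analysis.

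**Working it through.** **Inputs from the article.** n = 96 before attrition, two-sided 5% level, four covariates in the primary model, PV with no stated baseline subtraction, iAUC with the fasting level subtracted.

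**Inputs assumed, because the article gives none.** Fasting SD 0.45 mmol/L; SD of the peak rise 1.2 mmol/L; correlation r of 25(OH)D with fasting glucose from -0.1 to -0.4; rise unrelated to fasting level and to 25(OH)D; the four covariates unrelated to both.

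The plan states no figure for this regression. The sample size rests on a repeated-measures ANOVA, so there is no stated figure to reproduce here.

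**Step 1: correlation carried into PV.** Write PV = fasting + rise.

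- SD(PV) = √(0.45² + 1.2²) = √1.6425 = 1.28
- ρ = r × 0.45 / 1.28
- For r = -0.3: ρ = -0.135 / 1.28 = -0.105

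**Step 2: rejection rate.** The noncentrality is |ρ|√96 / √(1 - ρ²). For r = -0.3 this is 0.105 × 9.80 / 0.994 ≈ 1.04. There are 96 - 6 = 90 degrees of freedom (intercept, 25(OH)D and four covariates).

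| r | ρ with PV | Noncentrality | Rejection, closed form | Rejection, simulation |
|---|---|---|---|---|
| -0.1 | -0.035 | 0.34 | 6% | 6.5% |
| -0.2 | -0.070 | 0.69 | 10% | 9–11% |
| -0.3 | -0.105 | 1.04 | 18% | 16–17% |
| -0.4 | -0.140 | 1.39 | 28% | 25–27% |

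The simulations use the same SDs with a device error of SD 0.25 mmol/L. With fasting glucose added, PV rejects in 5–6%.

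**Step 3: sensitivity to the SDs.**

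- Fasting SD 0.7, r = -0.3: simulated rejection 29% without fasting glucose, 5% with it.
- Fasting SD 0.5, rise SD 1.0 to 1.5 (3000 runs per setting): 10–15% at r = -0.2, 17–27% at -0.3, 25–44% at -0.4; with fasting glucose, 5–6%.
- The same setting with a finger-prick error of SD 0.3: adjusted PV rejects in about 5–8%, because a noisy baseline removes the fasting component incompletely.
- With r = 0, adjustment lowers the standard error by about 4% (fasting SD 0.45) to 11% (fasting SD 0.7).

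**Step 4: the same check for iAUC.**

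- Rise unrelated to fasting level: iAUC rejects in 5–6% with or without fasting glucose.
- Rise increasing with fasting level (slope 0.5 to 1.0 mmol/L per mmol/L): iAUC rejects in 7–47% without fasting glucose and 4–6% with it.
- Rise unrelated to fasting level, error SD 0.3: adjusted iAUC rejects in about 5–9%, because the same noisy reading is both subtracted and adjusted for.

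The PV problem therefore needs only a link between 25(OH)D and fasting glucose. For iAUC, the rise must also depend on the fasting level.

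**The case against.** **Fasting glucose may be a mediator.** The article's Introduction cites trial evidence that "vitD supplementation may help reduce fasting plasma glucose concentrations", and describes vitamin D acting on insulin production and sensitivity. That places fasting glucose downstream of 25(OH)D. Adjusting for it would remove part of the total association, so leaving it out is defensible. This stands, and it is why the unadjusted model should be kept beside the adjusted one. The plan does not say which association it means.

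**The rates are not false positives for the outcome as worded.** A reader might infer from the table that the primary test has an inflated type I error. The documents do not support that: the outcome is the association with PV itself, and in these scenarios 25(OH)D is truly associated with PV through the fasting level. The rates are errors only if the result is read as an association with the postprandial rise.

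**The size of the link is unknown here.** The cited supplementation evidence concerns patients with type 2 diabetes, and this trial excludes diabetes. For healthy adults the article cites an association with insulin resistance, not with fasting glucose. Nothing in the article fixes a correlation for this population, and at -0.1 the effect on PV is slight.

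**Different covariate lists are not in themselves an error.** A group comparison and an exposure association can call for different sets. That is true in principle, but here the same variable is called a confounding factor for the same outcome in one model and omitted from the other without explanation.

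**iAUC.** A reader might extend the point equally to iAUC. The stated definition already removes the fasting level, so that extension needs a further assumption about the rise, and adjustment can add a small bias of its own.

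**Conclusion.** The point holds for PV. As planned, the primary PV slope combines any association of 25(OH)D with fasting glucose and any association with the rise, and it would be presented as postprandial. Under the base assumptions, with no association with the rise, this gives rejection in about 6–27% of trials for correlations of -0.1 to -0.4, against 5–6% with fasting glucose included. The figures are higher with a larger fasting SD or a smaller rise SD. All the SDs and correlations are assumptions, and PV is taken to be an absolute concentration because no subtraction is stated.

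The documents do not show that the unadjusted model is invalid, since it estimates a total association. Nor do they show that iAUC is affected to the same degree. The stated sample size is not touched. This is a cheap improvement to the meaning of one of the two primary measures.

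**What to change.** In Data analysis:

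1. Fit the PV regression on 25(OH)D with same-visit 0-min glucose added to age, gender, BMI and body fat percentage, pooled and within ethnic groups. Name this as the analysis that answers the postprandial question.
2. Report the PV model without fasting glucose beside it, labelled as the total association.
3. Keep the stated iAUC model, and use fasting-glucose adjustment for iAUC only as a sensitivity analysis.
4. State that PV is the absolute peak concentration, if that is what is meant.

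The fasting value is already collected at each visit. The cost is one degree of freedom, one more model to report, and an adjusted slope that excludes any effect of vitamin D acting through fasting glucose.
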